#### FPG, fasting insulin, and homeostasis model assessment of insulin resistance (HOMA-IR)

Improvements in insulin action are assessed by measurement of FPG and insulin levels, with subsequent calculation of HOMA-IR. Hemoglobin A_1c_ was not measured because it was not recommended for diagnosis of DM when the study began.

#### Dietary intake

Dietary intake is assessed with the Block Brief 2000 Food Frequency Questionnaire, which includes color photos representing portion sizes to aid participants in estimating typical portion size, and instructions ask participants to check off foods they have eaten during the past 3 months, indicating portion size and how often they eat each item.

#### Physical activity

Daily physical activity is assessed by the long version of the International Physical Activity Questionnaire (IPAQ) [27], which assesses activity over the past 7 days in the domains of occupation, transportation, yard/garden, household, leisure, and sitting. The IPAQ provides estimates of metabolic equivalent tasks energy expenditure, which can be reported for each activity or as a total score.

#### Utilization of weight loss resources

Participants rate how frequently they have used the following resources since their risk counseling session (*never, rarely, sometimes,* and *often*): written materials provided during the counseling session; MyHealtheVet, a website for veterans that offers health resources; other websites; home exercise equipment; books related to lifestyle changes; medication to prevent DM; weight loss medication; weight loss surgery; the VA’s MOVE! weight loss program; a personal trainer; a nutritionist; a weight loss program; recreation center or fitness facility; park or greenway; and physician-recommended regimen.

### Primary analysis

Primary analyses will be conducted on an intent-to-treat basis; participants will be analyzed in the group to which they were assigned, regardless of whether they attend the counseling session, using all available data [28]. Statistical analyses will be performed using SAS for Windows (Version 9.2: SAS Institute, Cary, NC) and R (http://www.R-project.org).

Our primary hypothesis is that mean weight loss in the CR + G group will be at least 6 lbs greater than in the CR + E group after 3 months. Weight is a continuous variable, and we will fit longitudinal models examining the short-term effects of the intervention using linear mixed models [29], where the baseline and 3-month weight measurements will be part of the outcome vector. This method handles dropouts in a principled manner. Depending on the type and scope of missing data, we will also explore multiple imputation as a strategy to use in conjunction with our primary analytic tools [30].

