## Methods/Design

### Study design and overview

The ongoing study is a two-arm RCT to determine the effect of genetic testing for DM on clinical outcomes and health behaviors. At baseline, participants provide written informed consent, information for conventional risk assessment, blood samples for fasting plasma glucose (FPG) and possible genetic testing, and baseline clinical and health behavior outcomes (Figure 1). Eligible participants are then randomized to receive conventional risk plus genetic test result counseling (CR + G) or conventional risk plus control eye disease counseling (CR + E), stratified by family history (unknown/low vs. moderate/high) and body mass index (BMI; < 35 vs. ≥ 35 kg/m^2^). Two to 4 weeks following baseline, all participants return for a risk counseling visit with a genetic counselor that does (CR + G) or does not (CR + E) include delivery of genetic test results and associated counseling. Psychological outcomes are assessed immediately following counseling and at 3 and 6 months. Behavioral and clinical outcomes are assessed at 3 and 6 months, with 3 months as the primary endpoint.

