### Randomization

Participants are randomized to the CR + G versus the CR + E arms in blocks within four strata defined by weight status (BMI <35 kg/m^2^ vs. ≥ 35 kg/m^2^) * family history of DM (unknown/low vs. moderate/high). We wanted to ensure balance in each arm on BMI status as weight trajectories, and adherence to recommendations may differ depending on severity of obesity. We also wanted to ensure balance on family history of DM in each arm as individuals with a strong family history may be more likely to engage in preventive lifestyle changes [9]. The project coordinator enters the values of the stratification variables and FPG into the study database, and the randomly assigned study arm is returned for eligible patients. Then, due to budget constraints, only blood samples for CR + G participants are sent for genetic testing.

Only the project coordinator and Master’s-level statistician have access to the randomization section of the study database. RAs are blind to arm assignment, and arm assignment is not revealed to participants or the genetic counselor until during the counseling session, after the conventional risk counseling has been delivered. Because randomization occurs prior to the genetic counseling session (to determine which blood samples will be extracted for genetic testing), participants are considered randomized whether or not they attend the counseling appointment and will be analyzed in an intent-to-treat manner.

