### Secondary analyses

The secondary hypotheses of this study are that mean perceived risk in the CR + G group will be greater than in the CR + E group immediately following counseling; that mean improvements in physical activity, caloric intake, and insulin resistance in the CR + G group will be greater than in the CR + E group after 3 months; and that mean improvements in weight loss, physical activity, caloric intake, and insulin resistance in the CR + G group will be greater than in the CR + E group after 6 months. Because all secondary outcomes are continuous, we will use the same analysis plan as for the primary outcome analysis. Hypotheses concerning perceived risk and the 3-month outcomes will be tested by the coefficient for the treatment × time interaction. For the hypothesis concerning 6-month outcomes, the models will include an additional time point. We will examine the treatment × time interaction, and, using contrasts among the model parameters, we will estimate the between-group differences after 3 and 6 months of follow-up. We expect the effect of the genetic testing to be largest at the 3-month time point because it is in closer proximity to the counseling session. A 6-month between-group difference that remains significant and is of similar magnitude to the 3-month difference would imply that the intervention effect was sustained.

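### The primary mixed model uses only baseline and 3-month weights; taking the 3-month contrast from the already planned three-time-point model is a cheap, modest improvement

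*Protocol article*

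**What the plan says.** The Primary analysis section of the protocol article promises intent-to-treat analysis of everyone randomized, "regardless of whether they attend the counseling session, using all available data". It then fixes the model for the primary outcome and adds a statement on dropouts: a linear mixed model "where the baseline and 3-month weight measurements will be part of the outcome vector. This method handles dropouts in a principled manner". Depending on the missing data, the authors add, "we will also explore multiple imputation as a strategy to use in conjunction with our primary analytic tools".

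Weight is also measured later. Under Study design and overview: "Behavioral and clinical outcomes are assessed at 3 and 6 months, with 3 months as the primary endpoint". The Secondary analyses section brings in the later measurement: "For the hypothesis concerning 6-month outcomes, the models will include an additional time point". Contrasts from that larger model are to give the between-group difference at 3 months as well as at 6.

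So two 3-month weight contrasts are planned. The primary one comes from the two-point model. The one that can use 6-month weights is secondary.

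**The concern.** A mixed model gains from incomplete participants only through post-baseline measurements that are correlated with the missing one. With an outcome vector of two weights there are none: whoever misses 3 months is left with a baseline weight that treatment cannot have affected. The model then gives practically the same answer as an analysis of covariance in 3-month attenders, and it needs the same assumption, that missingness depends on nothing beyond arm and baseline weight.

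That assumption could fail here. The Randomization section says "arm assignment is not revealed to participants or the genetic counselor until during the counseling session", so participants know their arm before the 3-month visit. Whether they come back could then depend on arm and on how their weight has gone since. At stake is some bias in the primary contrast that weights already being collected could partly remove.

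**Working it through.** **Inputs from the article (Power and sample size considerations):** SD 55 lb at 3 months, baseline to 3-month correlation 0.90, 300 per arm, 10% attrition (270 per arm seen at 3 months, 30 missed), two-sided α 0.05, difference 6 lb, power about 80%.

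**Assumed, because the article does not give them:** the 3-to-6-month correlation (0.90, 0.95, 0.97), the baseline-to-6-month correlation (0.85, 0.88, 0.89 respectively; 0.87 in step 5), the share of 3-month missers weighed at 6 months, and the missingness mechanism. Everyone seen at 3 months is taken to be seen at 6.

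**1. The plan's own power.**
- Analysis of covariance, as named: residual SD = 55 × √(1 − 0.9²) = 23.97. SE = 23.97 × √(2/270) = 2.063. Power = Φ(6/2.063 − 1.96) = 82.8%.
- Change score: SD = 55 × √(2 × 0.1) = 24.60. SE = 2.117. Power = 80.9%, which matches the stated figure.

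**2. What the 30 missers per arm add to the two-point model.** The article does not say whether baseline means are common to the arms, so both versions are shown.
- Common baseline mean: SE 2.0633 with or without them. They add exactly nothing.
- Separate baseline means: variance = 2 × 55² × [0.19/270 + 0.01/300] = 4.459, so SE = 2.1117, against 2.1170 in completers alone. The difference is 0.25%.

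**3. Precision if the 6-month weight is added.** Let r be the partial correlation of the 3- and 6-month weights given baseline, and m the number per arm seen at either visit. With a common baseline mean, variance = 2 × 55² × 0.19 × [(1 − r²)/270 + r²/m].
- Correlations 0.95 and 0.88, half return (m = 285): r = (0.95 − 0.9 × 0.88)/√(0.19 × 0.2256) = 0.763, r² = 0.582. SE = 2.032, power 84.0%.
- Best case, correlations 0.97 and 0.89, all return (m = 300): r² = 0.723. SE = 1.987, power 85.5%.
- Nobody returns (m = 270): SE 2.063, power 82.8%.

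The largest gain is 85.5 − 82.8 = 2.7 points. With separate baseline means it is 83.8 − 81.1 = 2.7.

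**4. Does the two-point model protect against anything?** Large-sample simulation with no true effect and about 9% to 11% missing. Missingness is related to weight in one arm only (log-odds 0.8 per SD), and correlations are 0.90, 0.95 and 0.88.

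| Missingness follows | Raw completer difference | Completer change score | Two-point model | Three-point model, all missers seen at 6 months |
|---|---|---|---|---|
| Baseline weight | −3.97 lb | +0.41 lb | about −0.03 lb | about −0.06 lb |
| Change to 3 months | −1.13 lb | −2.04 lb | −1.94 lb | −0.84 lb |

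In the first row the planned model removes the bias. In the second it is hardly better than completer change scores.

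**5. Bias in a deliberately adverse scenario.** About 14% are missing in CR + E, more likely with weight gain (odds ratio about 2.5 per SD of change), and 6–7% in CR + G, unrelated to outcome. There is no true effect; the 3-to-6-month correlation is 0.95 and baseline-to-6-month 0.87. Large-sample bias of the 3-month contrast, with CR + G made to look worse because CR + E gainers disappear:

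| Missers weighed at 6 months | Two-point | Three-point |
|---|---|---|
| none | about 2.7 lb | about 2.7 lb |
| one tenth | about 2.7 lb | about 2.6 lb |
| one third | about 2.7 lb | about 2.2 lb |
| one half | about 2.7 lb | about 1.8 lb |

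Six hundred simulated trials of the planned size per return rate show the same pattern: 2.55 against 1.99 lb at one third, and 2.76 against 1.91 lb at one half. The empirical SD is 2.10 against 2.08 and 2.12 against 2.10, so there is no precision penalty.

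**6. Milder mechanisms, two-point model.**
- Odds ratio 2.5 in both arms, 14% and 6.5% missing: about 1.5 lb.
- Odds ratio 1.5 in one arm, 14% and 6.5% missing: about 1.35 lb.
- Odds ratio 1.5 in one arm, 10% missing in each: about 0.9 lb.
- Same mechanism and 10% missing in both arms: about zero.

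**The case against.** The strongest reply is that the dropout sentence is not wrong. A likelihood model with baseline in the outcome vector is valid when missingness depends on arm and baseline weight, and step 4 shows that this protection is real. A reader might infer that the statement is empty. The article does not support that; the claim is only broader than the model can deliver. That analysis of covariance in attenders protects equally well does not make the method unprincipled.

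Second, the change does not help true dropouts. Someone gone by 3 months and not seen again has no 6-month weight. Only those who miss one visit and return contribute, and the article gives no return rate. This stands.

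Third, much is already planned: imputation is to be explored, and the three-point model with a 3-month contrast appears under Secondary analyses. A reader might take the two contrasts for a contradiction. They are not, because the article says which outcome vector is primary. But the imputation is conditional and names no predictors, and imputing from arm and baseline weight alone would repeat the two-point assumption. Naming predictors is commonly left to the analysis plan and is no fault here.

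Fourth, dropout driven by disappointment in the control arm is conjecture. Both arms receive personal conventional risk results, counseling of matched length, lifestyle counseling and the same visit payments. This also stands: differential missingness is possible, not shown.

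Finally, a primary test that uses data only up to the primary endpoint is defensible and can be reported sooner.

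**Conclusion.** The point holds as a cheap improvement, not as an error that invalidates the primary analysis. The two-point vector is fixed in the text, it gains essentially nothing from anyone without a 3-month weight, and it leaves out 6-month weights that a planned model would use.

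The gain is modest and conditional. Power rises by at most about 2.7 points. Bias is reduced only if 3-month missers return at 6 months and missingness follows the weight course differently by arm, and then only in part: in step 5, 1.8/2.7, or about two thirds, remains even when half return. If nobody returns, or missingness is unrelated to outcome or the same in both arms, the bias is unchanged.

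A reader might infer that the primary result will be off by 2 to 3 lb against the 6-lb target. The article does not support that. The mechanism, the attrition imbalance, the return rate and the correlations with the 6-month weight are all assumptions.

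**What to change.** In Primary analysis, state that the primary 3-month contrast comes from one linear mixed model with baseline, 3-month and 6-month weights in the outcome vector, with categorical time, unstructured covariance and arm × time. Use the same model for the weight contrasts in Secondary analyses, so that there is one 3-month estimate. If multiple imputation is done, include the 6-month weight as a predictor. Replace the general dropout statement with the assumption itself: missingness may depend on arm and on the weights observed in the model, and nothing further.

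This changes wording only and needs no new visits or measurements. Its cost is that the primary result waits for the 6-month visits, which are scheduled anyway. If the sponsor prefers to report at 3 months, the lesser step is to keep the two-point model, state its assumption (arm and baseline weight only), and name the 6-month weight as a predictor in any later imputation.

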### Secondary analyses

The secondary hypotheses of this study are that mean perceived risk in the CR + G group will be greater than in the CR + E group immediately following counseling; that mean improvements in physical activity, caloric intake, and insulin resistance in the CR + G group will be greater than in the CR + E group after 3 months; and that mean improvements in weight loss, physical activity, caloric intake, and insulin resistance in the CR + G group will be greater than in the CR + E group after 6 months. Because all secondary outcomes are continuous, we will use the same analysis plan as for the primary outcome analysis. Hypotheses concerning perceived risk and the 3-month outcomes will be tested by the coefficient for the treatment × time interaction. For the hypothesis concerning 6-month outcomes, the models will include an additional time point. We will examine the treatment × time interaction, and, using contrasts among the model parameters, we will estimate the between-group differences after 3 and 6 months of follow-up. We expect the effect of the genetic testing to be largest at the 3-month time point because it is in closer proximity to the counseling session. A 6-month between-group difference that remains significant and is of similar magnitude to the 3-month difference would imply that the intervention effect was sustained.

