### Measures

Demographics are assessed at baseline by an RA. Psychological outcomes are assessed by the genetic counselor immediately following the risk counseling. The remaining outcomes are assessed by a blinded RA at 3 and 6 months, with 3 months as the primary endpoint. Participants receive $25 for the 3- and 6-month outcome visits.

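### The perceived-risk hypothesis is tested by a treatment × time interaction, which needs a pre-counseling value that the stated schedule does not provide

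*Protocol article*

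**What the plan says.** All references are to the protocol article.

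- **Hypothesis (Secondary analyses).** It is a difference in level at one time: "mean perceived risk in the CR + G group will be greater than in the CR + E group immediately following counseling". The other hypotheses listed with it concern improvement, that is, change.
- **Test (same section).** "Hypotheses concerning perceived risk and the 3-month outcomes will be tested by the coefficient for the treatment × time interaction".
- **Model (same section).** "Because all secondary outcomes are continuous, we will use the same analysis plan as for the primary outcome analysis". Under Primary analysis that plan is a linear mixed model "where the baseline and 3-month weight measurements will be part of the outcome vector".
- **Schedule (Study design and overview).** Among outcomes, the baseline list contains "baseline clinical and health behavior outcomes" and no psychological outcomes. It then says: "Psychological outcomes are assessed immediately following counseling and at 3 and 6 months".
- **Schedule (Measures).** "Psychological outcomes are assessed by the genetic counselor immediately following the risk counseling". Then: "The remaining outcomes are assessed by a blinded RA at 3 and 6 months, with 3 months as the primary endpoint".
- **Baseline visit.** After the numeracy measure, the research assistant gives the remaining measures orally. The section does not list them.

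The perceived-likelihood item, scored 1 to 7, is described under Psychological outcomes.

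**The concern.** A treatment × time interaction is a difference between arms in change from one visit to another. The hypothesis is about a difference in level at a single visit. The two coincide only if one of the visits precedes counseling, when randomization makes the expected gap zero. The sections that schedule psychological outcomes start them at the counseling visit.

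If that schedule is complete, the named coefficient does not address the hypothesis. A gap that appears at counseling and lasts would give an expected interaction of zero. A gap that fades would give a coefficient whose sign is opposite to the hypothesis. Perceived risk is the first secondary hypothesis listed, so its test should be unambiguous.

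**Working it through.** **1. The plan's own figure.** None is given for perceived risk. The only power statement is for weight: SD 55 lb, correlation 0.90, 300 per arm, 10% attrition, about 80% power for 6 lb.
- Analysed per arm: 300 × 0.9 = 270.
- Residual SD: 55 × √(1 − 0.90²) = 23.97 lb.
- SE: 23.97 × √(2/270) = 2.06 lb.
- Power: Φ(6/2.06 − 1.96) ≈ 83%, in line with the rounded statement.

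The present point does not depend on this figure; it only supplies the 270 used below.

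**2. What the interaction estimates.** Let g0, g1 and g3 be the CR + G minus CR + E gaps before counseling, right after it and at 3 months. The hypothesis is g1 > 0.

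| Visits in the model | Interaction coefficient | Does it test g1? |
|---|---|---|
| Post-counseling only | Not estimable: intercept, treatment, time and interaction have rank 2 of 4 | No |
| Post-counseling and 3 months | g3 − g1 | No: 0 if the gap lasts, negative if it fades |
| Baseline and post-counseling | g1 − g0, with g0 = 0 in expectation | Yes |

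In the second row the term that answers the hypothesis is the treatment effect at the post-counseling visit, not the interaction.

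**3. Which row applies.** The sections point in different directions.
- The overview names the classes of outcome taken at baseline and leaves psychological outcomes out. This favours the first or second row.
- The Measures section mentions no baseline either, but it also omits one for weight, which the primary model requires. Its silence is weak evidence.
- The Baseline visit section may cover perceived risk. It cannot mean every instrument in the study: the questionnaire on reactions to genetic testing is given only in CR + G at 3 and 6 months, and resource use is asked with reference to the time since counseling.
- The carried-over primary model has baseline in the outcome vector, which suggests the third row. The reason given for carrying it over is that the outcomes are continuous, which does not show that a baseline value exists.

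No section states a pre-counseling perceived-risk measurement, and none rules one out.

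**4. Illustrative size.** Assumptions not in the document: g1 = 0.25 SD, 270 per arm at each visit, within-person correlation r of 0.3, 0.5 or 0.7, two-sided α of 0.05.
- Direct contrast: SE = √(2/270) = 0.0861 SD; power = Φ(0.25/0.0861 − 1.96) = 83%.
- Interaction: SE = √(2(1 − r)) × √(2/270), which is 0.102, 0.086 and 0.067 SD.

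| Test | Expected coefficient (SD) | Rejection at r = 0.3 / 0.5 / 0.7 |
|---|---|---|
| Direct contrast after counseling | 0.25 | 83% (r not used) |
| Interaction, baseline to post-counseling | 0.25 | 69% / 83% / 96% |
| Interaction, post-counseling to 3 months, gap fully kept | 0 | 5% / 5% / 5% |
| Same, three quarters kept | −0.0625 | 9% / 11% / 16% |
| Same, half kept | −0.125 | 23% / 31% / 47% |

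Rejections in the last two rows are almost all in the direction opposite to the hypothesis.

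**The case against.** The strongest reply is that the analysis section presupposes a baseline. Secondary outcomes inherit a model with baseline in the outcome vector, so for a hypothesis dated to the counseling visit the natural model is baseline plus post-counseling. The named coefficient is then valid, and by the table above it is as powerful as the direct contrast at r = 0.5 and more powerful at r = 0.7. The timing sentences read as descriptions of follow-up, since they omit baseline even for weight. The study-overview figure is not shown and may settle the matter.

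Much of this stands. A reader might infer that perceived risk has no baseline value and that the test is therefore wrong outright. The documents do not support that: the evidence is an omission from one overview sentence, set against wording elsewhere that could include the item. The 5% rejection rate likewise belongs to a post-counseling to 3-month model, which the article does not explicitly propose for this hypothesis.

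What the reply does not remove is the mismatch. The overview lists the outcome classes taken at baseline and omits this one, while the named test needs it. The article itself fixes both the schedule and the test, so this is more than detail left to a fuller document.

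**Conclusion.** The point holds as an inconsistency between schedule and test, to be resolved by clarification. If perceived risk is not measured before counseling, the named interaction is inestimable or tests later change in the gap. If it is measured, the test is sound and the overview and Measures sections should say so. Some text needs correcting in either case.

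The reach is limited to one secondary hypothesis. The primary weight analysis and its power statement are untouched. All power figures for perceived risk are illustrative, because the article gives no SD, effect or correlation for the item. A reader might also infer that a fading gap would be reported as support for the hypothesis. That does not follow, because the coefficient would have the wrong sign.

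**What to change.** 1. In Secondary analyses, define the perceived-risk test as the model-based CR + G minus CR + E contrast at the post-counseling visit. This is correct whether or not a baseline exists. The same section already uses model contrasts for the 3- and 6-month differences.
2. If perceived risk is collected at baseline, use that value in the model for this contrast.
3. Reconcile Study design and overview, Baseline visit, Measures and Secondary analyses on whether it is collected before counseling.
4. Keep any interaction from post-counseling to 3 or 6 months only as a description of how the gap evolves.

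The cost is about one sentence of analysis wording plus the schedule clarification. No new data are needed, and the sample size does not change.

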### Power and sample size considerations

We plan to enroll 300 participants in each arm of the study (total n = 600). Our power calculation is based on our primary outcome of weight, under the null hypothesis that there will be no between-group difference in weight at the 3-month time point. The sample size is based on methods appropriate for analysis of covariance analyses in randomized trials [31], where we applied a two-sample *t*-test sample size calculation for the between-group difference at the 3-month time point multiplied by a factor 1-(*rho*)^2^, where *rho* represents the Pearson correlation between baseline and 3-month time point outcome measures.

Based on our prior work [32], we estimated a standard deviation of approximately 55 lbs at the 3-month time point and a correlation of 0.90 between baseline and 3-month weights. Using these variability and correlation estimates, and assuming an attrition rate of 10% at 3 months with an α = 0.05 (two-sided) and sample size of 300 per group, we will have approximately 80% power to detect a 6-lb difference in weight between the CR + G and CR + E groups. A 6-lb difference is considered clinically meaningful [33] based on evidence from the Finnish Diabetes Prevention Study, in which a net weight loss of 7.5 lbs at 1 year reduced risk for DM by 58%.

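### The stated basis for calling the effect sustained does not estimate the 3-to-6-month change in effect, so it can license that claim for a substantially decayed effect

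*Protocol article*

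**What the plan says.** All of this is in the Secondary analyses section of the protocol article. On the 6-month outcomes: "For the hypothesis concerning 6-month outcomes, the models will include an additional time point". The treatment-by-time interaction is examined and, "using contrasts among the model parameters, we will estimate the between-group differences after 3 and 6 months of follow-up". The authors anticipate a declining effect: "We expect the effect of the genetic testing to be largest at the 3-month time point". They then say what they would take as persistence: a 6-month difference that "remains significant and is of similar magnitude to the 3-month difference would imply that the intervention effect was sustained".

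No tolerance is attached to the comparison of magnitudes, and the difference between the two between-group differences is not named as the quantity behind the inference. Power is given for weight at 3 months only (Power and sample size considerations): "we will have approximately 80% power to detect a 6-lb difference in weight between the CR + G and CR + E groups".

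**The concern.** Whether an effect was sustained is a question about how the treatment effect changes between 3 and 6 months. Significance at 6 months answers a different question: whether any effect exists at that visit. The comparison of magnitudes points the right way, but as written it sets one point estimate beside another with no stated interval or tolerance.

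This matters because the authors themselves expect the effect to be largest at 3 months. The criterion will therefore be applied where partial decay is plausible, and there it has to separate partial loss from persistence. If it is followed as written, a trial could report a sustained effect after much of the 3-month difference has gone, and readers would not see how imprecisely the change was measured.

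**Working it through.** **Inputs from Power and sample size considerations.** SD: "we estimated a standard deviation of approximately 55 lbs at the 3-month time point". Correlation: "a correlation of 0.90 between baseline and 3-month weights". Sample: "assuming an attrition rate of 10% at 3 months with an α = 0.05 (two-sided) and sample size of 300 per group", so 300 × 0.90 = 270 evaluable per arm.

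**Assumed, because the article does not give them.** SD of 55 lb at 6 months; baseline-to-6-month correlation 0.85–0.90; 3-to-6-month correlation 0.90–0.97; 270 per arm at 6 months as well; similarity read as a 6-month/3-month ratio of at least 0.50, 0.67 or 0.80.

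**Step 1: the article's own figure.** The baseline-adjusted SD is 55 × √(1 − 0.90²) = 23.97 lb, and SE = 23.97 × √(2/270) = 2.06 lb. Power for 6 lb is 82.8%. A change-score version, SD = 55 × √(2 × 0.10) = 24.60 lb, gives 80.9%. Both fit the stated approximate 80%, so the inputs are usable.

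**Step 2: precision of the change in effect.** Write r06 and r36 for the baseline-to-6-month and 3-to-6-month correlations. Given baseline, the variance is 55²(1 − 0.90²) at 3 months and 55²(1 − r06²) at 6 months, with covariance 55²(r36 − 0.90·r06). For r06 = 0.90 and r36 = 0.95:

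- each variance is 3025 × 0.19 = 574.75, and the covariance is 3025 × 0.14 = 423.5;
- the variance of the change is 2 × 574.75 − 2 × 423.5 = 302.5, so the SD is 17.39 lb;
- SE of the contrast = 17.39 × √(2/270) = 1.50 lb, and the 95% half-width is 1.96 × 1.50 = 2.9 lb.

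Over all the assumed correlations the SE runs from 1.16 to 2.12 lb (half-width 2.3–4.1 lb). With r36 limited to 0.92–0.95 and 6-month attrition of 10–20%, the half-width is 2.9–4.1 lb.

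**Step 3: what the criterion lets through.** In the central case a 6-month estimate is significant once it exceeds 1.96 × 2.06 = 4.04 lb. If the true 6-month effect is 3 lb, the standardised distance is (4.04 − 3)/2.06 = 0.51, so about 31% of all trials are significant at 6 months. Simulating both estimates jointly (400,000 draws per scenario), among trials significant at 3 months with a true 3-month effect of 6 lb, the share meeting both conditions is:

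| True effect at 6 months | ratio ≥ 0.50 | ratio ≥ 0.67 | ratio ≥ 0.80 |
|---|---|---|---|
| 4 lb | 42–59% | 37–46% | 23–28% |
| 3 lb | 26–36% | 18–22% | 5–15% |

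Reading similarity as within 2 lb instead (r36 0.92–0.95, 6-month attrition 10–20%) passes the halved effect in about 14–17%.

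**Step 4: what the interval would show.** Take hypothetical estimates of 6 lb at 3 months and 4.5 lb at 6 months in the central case. The 6-month difference is significant (4.5/2.06 = 2.18) and the ratio is 0.75. The change is −1.5 lb, with 95% CI −1.5 ± 2.9, or −4.4 to +1.4 lb. Those data are compatible with full persistence and with the loss of more than two thirds of the effect (4.4/6 = 0.73). The criterion as written does not call for that interval.

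**The case against.** The strongest reply is that the sentence is a closing interpretive remark on a secondary question, not a formal test. Durability is not among the listed secondary hypotheses. The planned model already contains the 6-minus-3-month contrast, and the magnitude clause is itself a guard against decay. A numerical tolerance could sit in an analysis plan that is not shown. Much of this stands. It makes the point minor, and the missing tolerance alone would not be a finding. What remains is that the article does state a basis for the inference, and that basis is not the estimated change with its uncertainty.

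A reader might also infer that the wording would miss a truly sustained effect. With 6 lb at both visits and a significant 3-month result, 6-month significance fails in about 7–25% of trials. The article does not support calling those errors. It gives a sufficient condition for persistence and nowhere says that a non-significant 6-month result means the effect was lost. In those trials it makes no durability claim.

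A third objection is that the contrast is imprecise too. That is correct. As a difference test it detects a fall from 6 to 3 lb with only 29–73% power. Requiring its CI to exclude a 3-lb loss would confirm a fully sustained 6-lb effect in only 29–74% of trials, while passing the halved effect 2.5% of the time. That trades sensitivity for specificity, so a compulsory margin does not follow from this point. With a ratio of at least 0.67, the criterion is met while the contrast shows significant decay in at most about 6% of trials. The gain is therefore mainly in showing the uncertainty, not in overturning conclusions.

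**Conclusion.** The concern holds in one direction and is minor. The stated basis for inferring persistence can license that claim for a substantially decayed effect: roughly 5–36% of trials significant at 3 months when a 6-lb effect halves. The width of that range comes mostly from the undefined reading of similarity and otherwise from the assumed correlations, so the article supports no single error rate. The figures also assume an SD of 55 lb at 6 months and, for this range, 10% attrition still holding then. They concern weight; the article gives no inputs for the other secondary outcomes. The primary endpoint, primary test and sample size are unaffected. The stronger reading, that a sustained effect would be wrongly declared lost, is not supported by the text.

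**What to change.** Replace the closing sentence of Secondary analyses with wording such as: *Any statement about durability will rest on the 6-month between-group difference minus the 3-month between-group difference, estimated from the three-time-point model and reported with its 95% confidence interval. Statistical significance at 6 months will not on its own be taken as evidence for or against durability.*

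The team may also pre-state how much loss would still count as sustained, before 6-month results by arm are seen. If so, it should accept that requiring the interval to exclude that loss would often leave durability undetermined.

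The cost is one sentence and one extra contrast from a model already planned, with no new data. The likely consequence is more cautious wording, because an interval of about ±3–4 lb around the change is wide against a 6-lb target effect.
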